#### Nasopharyngeal carriage outcome measures

NP carriage of pneumococcal serotypes is measured by traditional culture (colonial morphology, α-haemolysis, the optochin test and *lytA* PCR where indicated)^36^ and latex agglutination using type-specific antisera at 2, 6, 9 and 12 months of age in all groups and at 18 and 24 months of age in the control groups (arms F and G). NP carriage and density of pneumococcal serotypes are measured by quantitative real-time PCR (qPCR) targeting *lytA* and microarray at 18 and 24 months of age.^37 38^ Overall, capsular, vaccine-type and serotype-specific carriage rates are described. The antimicrobial resistance of pneumococcal isolates is determined at 12 months of age by the Clinical and Laboratory Standards Institute (CLSI) disk diffusion method, for oxacillin, erythromycin, trimethoprim/sulfamethoxazole, ofloxacin, clindamycin, vancomycin, tetracycline and chloramphenicol. E-tests are conducted for penicillin, ceftriaxone and vancomycin where indicated, and CLSI breakpoints applied.NP carriage of *H. influenzae* is measured by traditional culture (colonial morphology, X and V dependence, *SiaT* PCR for discrimination from *H. haemolyticus* and the Phadebact Haemophilus coagglutination test) at 12 months of age in all groups, at 6 and 9 months of age in arms A and C, and from all swabs in the control groups (arms F and G). Overall density of *H. influenzae* carriage is measured by qPCR targeting *hpd* and *SiaT* diagnostic targets at 18 and 24 months of age.^39 40^

#### Immunogenicity of *Infanrix-hexa*

Immunogenicity of *Infanrix-hexa* is measured in terms of IgG levels to diphtheria, tetanus, Hib PRP antigen, hepatitis B surface antigen and *Bordetella pertussis*. IgG levels will be determined by ELISA, using commercial test kits.

An overview of the procedures for collection, transportation and laboratory analyses of the blood and NP samples can be found in online supplementary appendix 1.

10.1136/bmjopen-2017-019795.supp1Supplementary file 1

### Sample size

The target sample size for infant recruitment (groups A–F) is 1200 with an allocation ratio of 3:3:5:4:5:4, resulting in target group sizes of A=150, B=150, C=250, D=200, E=250 and F=200. An additional target of 200 children aged 18 months are recruited into group G. Sample size calculations are based on the primary outcome of post-primary series immunogenicity (proportion of participants with serotype-specific antibody concentrations ≥0.35 µg/mL) for each of the two study questions. A non-inferiority margin of a 10% difference in absolute risk is deemed clinically significant, as used by regulatory authorities. Non-inferiority is assessed for each of the 10 serotypes in PCV10 (comparing groups A+B with group C or group E), and an overall conclusion of non-inferiority is drawn if the alternative hypotheses are accepted for at least 7 of the 10 serotypes. This sample size provides >99% power for the overall conclusion of non-inferiority with a 5% one-sided type I error rate, estimated by simulation using a tailor-made program written for implementation in Stata with 10 000 replications.^41^ Powers for serotype-specific hypotheses range from 83% to >99%, calculated in PASS Software 2002 using the Farrington-Manning (1990) method.^42^ Based on findings from our earlier work in Fiji and from data available in the literature,^43–45^ the assumed probabilities of antibody concentration ≥0.35 µg/mL are 95% for serotypes 1, 4, 5, 7F, 9V, 14 and 19F; 90% for serotype 18C; 80% for serotype 23F; and 75% for serotype 6B. The within-subject correlation between the multiple binary endpoints is captured by a subject-level variation term with SD 1.7 in a random-effect logistic regression model, and the loss to follow-up rate is assumed to be 5% post-primary series and 10% at 12 months of age. The sample size also provides 98% power to detect a difference in post-primary series immunogenicity following two doses of PCV10 or PCV13, defined by a 10% difference in absolute risk based on Fisher’s exact test (5% two-sided).

#### Carriage outcomes

The sample size provides 76% and 71% power to detect a difference in NTHi carriage rates at 12 months of age between groups A and F and groups A and B, respectively, and 64% and 59% power to detect a difference in vaccine-type pneumococcal carriage rates between groups A and F and groups A and B, respectively. Difference in carriage is defined by a relative risk of 0.6. The calculations were based on Fisher’s exact tests (5% one-sided), assuming carriage rates in group F (controls) of 30% for NTHi and 24% for vaccine-type pneumococci, based on data from Vietnam ([name], personal communication).

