Carriage of pneumococci in the nasopharynx is commonly a prerequisite for IPD and is the usual means of transmission of the bacteria. The herd effect of pneumococcal vaccination is mediated by the impact on NP carriage.^23^ Vaccination with PCVs generally results in a decrease in vaccine type (VT) pneumococcal carriage, which is most commonly observed after a booster dose and often accompanied by a compensatory increase in non-VT carriage.^23–27^ There have been few trials that evaluate the effect of different PCV schedules on carriage. A trial from the Netherlands showed that a two-dose primary series with or without a booster reduced VT carriage at 12 months of age compared with controls.^28^ VT carriage was further reduced at 18 months in the group that received the booster dose, compared with the group that did not receive the booster, although this difference did not persist at 24 months of age. Similarly, our trial in Fiji showed that a two-dose or three-dose primary series with or without a booster reduced VT carriage at 12 months of age compared with controls, but no difference was seen at 17 months of age ([name], personal communication).

It has been hypothesised that the protein D carrier in PCV10 may result in an impact on *H. influenzae* carriage. A recent review of the impact of protein D-containing PCVs on NTHi carriage concludes that any such impact is likely to be small and transient, although changes in the density of carriage are yet to be evaluated. Two large phase III trials (POET trial of an 11-valent PCV and COMPAS trial of PCV10) showed trends towards a reduction in NTHi carriage following a booster dose of PCV, along with a trial of PCV10 in toddlers in Kenya, but other trials conducted in Finland, the Netherlands and the Czech Republic showed no impact of PCV10 on NTHi carriage.^29^

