### Statistical methods

#### Analysis of primary and secondary outcomes

For each of the two study questions, the primary objective is to compare a 2+1 schedule of (1) PCV10 and (2) PCV13, with a 3+1 schedule of PCV10. The primary outcome is the proportion of participants with serotype-specific antibody concentrations ≥0.35 µg/mL, 4 weeks post-primary series (at 5 months of age). Data from arms A and B are combined to form the three-dose post-primary series group. The primary analyses assess the non-inferiority of (1) two doses of PCV10 at 2 and 4 months of age (arm C) compared with three doses at 2, 3 and 4 months of age (arms A+B); and (2) two doses of PCV13 at 2 and 4 months of age (arm E) compared with three doses of PCV10 at 2, 3 and 4 months of age (arms A+B). The proportion of children achieving protective levels of serotype-specific IgG (≥0.35 µg/mL) 4 weeks post-primary series is determined for each of the 10 PCV10 serotypes. The non-inferiority margin is defined by a 10% difference in absolute risk. The serotype-specific risk differences (arms A+B/arm C) with 90% CIs are calculated using the Newcombe Score method and the null hypothesis rejected if the upper bound of the CI is <10%. Overall non-inferiority is declared if at least 7 of the 10 individual null hypotheses are rejected at a one-sided 5% level of significance. Secondary data analyses to address the primary objective include the ratio of GMCs post-primary series (arm C/arms A+B and arm E/arms A+B) with 95% CIs, and the booster response analysed by analysis of covariance, adjusting for pre-booster levels.

#### Analysis of key secondary objectives for study question 1

A single dose of PCV10 at 2 months of age (arm D) will be assessed for non-inferiority to three doses at 2, 3 and 4 months of age (arms A+B), as described for the primary objective.The impact of a booster dose on pneumococcal and NTHi carriage will be assessed at 12 months of age. Overall pneumococcal, capsular pneumococcal, PCV10 type and NTHi carriage rates will be determined. Proportions will first be compared between the 3+1 group (arm A) and the control group (arm F), using Fisher’s exact test. Where significant differences are found, rates will then be compared between the 3+0 group (arm B) and controls and between the 3+1 and 3+0 groups.

#### Analysis of key secondary objectives for study question 2

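### The stated 71% and 59% power for the booster effect on carriage (A versus B) leaves out the plan's own test order; on its own assumptions the power is about 60% and 46%

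*Protocol article*

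**What the plan says.** **Power (Sample size, Carriage outcomes).** In each pair of figures the first is for A versus F and the second for A versus B. For NTHi: "The sample size provides 76% and 71% power to detect a difference in NTHi carriage rates at 12 months of age between groups A and". For vaccine-type pneumococci: "64% and 59% power to detect a difference in vaccine-type pneumococcal carriage rates between groups A and F and groups A and B, respectively". The effect is fixed by "Difference in carriage is defined by a relative risk of 0.6". The calculations use Fisher's "exact tests (5% one-sided), assuming carriage rates in group F (controls) of 30% for NTHi and 24% for vaccine-type pneumococci". No carriage rate is given for arm B.

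**Numbers (Sample size).** The allocation is described as "resulting in target group sizes of A=150, B=150, C=250, D=200, E=250 and F=200", with 10% loss assumed by 12 months.

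**Test order (Statistical methods, key secondary objectives for study question 1).** Carriage at 12 months is compared first between arm A (3+1) and arm F (controls). Then: "Where significant differences are found, rates will then be compared between the 3+0 group (arm B) and controls". Arm A against arm B belongs to this same conditional second step.

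**Objective (Key secondary objectives, study question 1).** The booster effect on carriage is to be assessed by comparing A with B and A with F.

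**The concern.** The two sections do not describe the same procedure. The power section treats A versus B as a test that is always made. The analysis section makes it only after A versus F has succeeded. A real booster effect can therefore go undetected in two ways: A versus F fails and A versus B is never tested, or A versus B is tested and fails. The stated 71% and 59% count only the second.

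Arms A and B share the same three-dose primary series, so A versus B is the contrast that isolates the booster. If its power is overstated, a null or untested result may be read with more confidence than the design supports.

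Arm B's rate is a further question. The stated figures appear to give 3+0 children the unvaccinated rate, while Background and rationale reports from an earlier Fiji trial that "a two-dose or three-dose primary series with or without a booster reduced VT carriage at 12 months of age compared with controls".

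**Working it through.** **Inputs.** Group sizes after 10% loss: A = 150 × 0.9 = 135, B = 150 × 0.9 = 135, F = 200 × 0.9 = 180. Control carriage: 30% (NTHi), 24% (vaccine type). Arm A at relative risk 0.6: 0.6 × 30% = 18%; 0.6 × 24% = 14.4%. Tests: Fisher's exact, one-sided 5%.

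**Step 1: reproduce the stated power.** Let R(a, c) = 1 if the one-sided Fisher p-value for a carriers in arm A and c in the comparator is at most 0.05, and 0 otherwise. Then

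power = Σ_a Σ_c Bin(a; 135, p_A) · Bin(c; n_C, p_C) · R(a, c).

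| Comparison | NTHi | Vaccine type | Stated |
|---|---|---|---|
| A vs F (135 vs 180) | 75.7% | 64.0% | 76%, 64% |
| A vs B (135 vs 135), B at control rate | 70.7% | 58.6% | 71%, 59% |

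All four figures agree after rounding. Other versions of A versus B do not match:

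| A vs B variant | NTHi | Vaccine type |
|---|---|---|
| No loss (150 vs 150) | 75.0% | 63.2% |
| 5% loss (142 vs 142) | 72.8% | 60.5% |
| Two-sided Fisher | 58.5% | 46.0% |
| Normal approximation | 74.9% | 64.1% |
| B/F = 0.8, A/B = 0.6 | 58.6% | 47.9% |

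The stated figures are therefore stand-alone powers, with arm B apparently at the control rate.

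**Step 2: apply the test order.** A versus B is reached only if A versus F is significant, which fails in 1 − 0.757 = 24% (NTHi) and 1 − 0.640 = 36% (vaccine type) of trials under the planned effect. The probability that both tests succeed, with arm A shared, is

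joint power = Σ_a Bin(a; 135, p_A) · [Σ_f Bin(f; 180, p_F) R_F(a, f)] · [Σ_b Bin(b; 135, p_B) R_B(a, b)].

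With B at the control rate this gives 59.8% (NTHi) and 45.6% (vaccine type). The shortfalls from the stand-alone values are 70.7 − 59.8 = 10.9 points and 58.6 − 45.6 = 13.0 points. The joint values exceed the simple products (0.757 × 0.707 = 0.535; 0.640 × 0.586 = 0.375) because the shared arm A makes the two tests positively correlated.

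**Step 3: vary arm B's rate.** The result depends on which ratio stays at 0.6. Joint power, one-sided 5%:

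| B/F | A/B = 0.6: NTHi | A/B = 0.6: vaccine type | A/F = 0.6: NTHi | A/F = 0.6: vaccine type |
|---|---|---|---|---|
| 1.00 | 59.8% | 45.6% | 59.8% | 45.6% |
| 0.95 | 60.9% | 47.0% | 52.6% | 39.7% |
| 0.90 | 60.8% | 47.4% | 44.2% | 33.2% |
| 0.85 | 59.6% | 47.0% | 35.2% | 26.5% |
| 0.80 | 57.6% | 45.9% | 26.3% | 20.0% |

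With A/B held at 0.6, a lower arm B rate hardly matters: the first test gets easier as the second gets harder. With A/F held at 0.6, the booster effect itself shrinks; at B/F = 0.8 it is A/B = 0.6/0.8 = 0.75.

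**The case against.** The strongest reply is that the stated figures are correct per-comparison powers and the section does not claim to give power for a sequence. That is fair as to arithmetic: nothing was miscalculated. But the plan never makes A versus B as an unconditional test, so the stand-alone figure is not the power of the planned analysis.

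A second reply is that low power is already disclosed. The strengths and limitations list does say that power for carriage is relatively low, but it ties the risk to carriage rates below those anticipated. The shortfall here is present even if carriage is exactly as assumed.

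A third is that these are secondary outcomes and the trial is sized on immunogenicity. That stands and limits the weight of the point.

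Four stronger readings are tempting, and the document does not support them:

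- *That 60% and 46% are upper limits.* They are the values with B at the control rate. With A/B at 0.6 the joint power peaks near 61% and 47%.
- *That the real power is 26% and 20%.* That scenario replaces the planned relative risk by A/B = 0.75, and any test loses power against a smaller effect. B/F = 0.8 is illustrative and has no source in the article.
- *That the assumed arm B rate contradicts the sponsor's own evidence.* The Fiji carriage result is a personal communication without an effect size, and the article describes that trial as using PCV7 and a polysaccharide booster. It makes some primary-series effect on vaccine-type carriage plausible, no more. For NTHi, the same section expects any effect of this class of vaccine to be small and transient, so a rate near control is reasonable.
- *That the ordering is wrong and must go.* Testing 3+1 against controls first is a recognised hierarchical approach. A versus F is itself part of the objective, and four carriage measures are listed for this analysis.

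**Conclusion.** The point holds as a mismatch between the stated power and the planned analysis. On the plan's own assumptions, the power to show the booster effect through A versus B is about 60% for NTHi and 46% for vaccine-type carriage, against 71% and 59% stated. For vaccine-type carriage it falls below one half. Across B/F from 0.8 to 1.0 with A/B at 0.6, the ranges are about 58–61% and 46–47%. Only if the booster effect is smaller than planned does power drop much further.

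This rests on three readings. Arm B's rate is inferred from the match in step 1. The condition on A versus F is applied separately to each carriage outcome. The tests are one-sided at 5%, as in the sample size section; the analysis section does not state sidedness for carriage, and two-sided tests throughout, with B at the control rate, would give 47% and 34%.

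The primary outcome, its sample size and its conclusions are unaffected. The correction is worth making because the booster effect on carriage is a key secondary objective.

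**What to change.** In Carriage outcomes:

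- Restate the A versus B power as the joint probability that A versus F and A versus B are both significant: about 60% (NTHi) and 46% (vaccine type). The stand-alone 71% and 59% may remain beside these if labelled as such.
- State the carriage rate assumed for arm B.
- Show the joint power over a range of arm B rates, for example B/F from 0.8 to 1.0, saying whether A/B or A/F is held at 0.6.

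The cost is less favourable figures and a few lines of text. No participants, visits or analyses are added.

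Testing A versus B without first requiring a significant A versus F is an option, not a required correction. It would restore the stand-alone power of 71% and 59% (with B at the control rate) but give up the error control that the ordering provides across the carriage measures. The sponsor should weigh that trade-off.

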### Recruitment

Participants in groups A–F are recruited from infants born in the study communes during the enrolment period. Commune health centre staff identify potential participants from the commune health centre birth records. Based on the expected number of births, around a quarter of infants born in the study communes need to be enrolled to complete recruitment within the target enrolment period of 12 months. Recruitment rates will be monitored on a monthly basis and meetings held with study staff and commune health centre staff to discuss any significant declines in recruitment rates. Commune health centre staff visit the home of potential participants when the infant is approximately 6 weeks old and provide verbal and written information about the trial, in Vietnamese. Those interested in participating are referred to the study clinic when the infant is approximately 2 months old. At this time, written informed consent is obtained (online supplementary appendix 2), after which a study nurse/doctor examines the infant to ensure that all the eligibility criteria are met. Participants in group G are recruited from children turning 18 months old in the study communes in parallel to the children in groups A–F turning 18 months.

10.1136/bmjopen-2017-019795.supp2Supplementary file 2

### Allocation

The allocation sequence for groups A–F is produced using a computer-generated list of random numbers using a block randomisation scheme, stratified by district. The group allocation is contained within a sealed envelope at the study clinic, with sequential ID numbers written on the outside of the envelope. The allocation sequence is generated at Menzies School of Health Research. A study doctor will enrol participants and assign them to a study group by selecting the next available envelope. The envelope is not opened until after completion of the informed consent and eligibility assessment processes.

### Blinding

All laboratory staff are blinded to the study group allocation as the key outcome measures that address the study objectives are all laboratory based. Laboratory samples are labelled with the ID number, which does not identify the study group. Given the different timing of the vaccination schedules in the different groups, the study nurses, vaccine administrators and participants will not be blinded to the study group allocation.

### Data collection methods

Standardised carbon copy data collection forms are used and are completed by dedicated, trained study staff. The original is transported to the trial office for data entry, with the carbon copy filed at the clinic. Blood samples and NP swabs are collected by staff specifically trained in the collection of samples from infants, and the volume of blood collected and the swab quality are recorded.

Retention: Appointments are documented on a parent-held health record card and a reminder phone call made the week before the scheduled visit. If a participant fails to attend an appointment, a follow-up phone call is made to rebook the visit. Participants are given a small payment towards the transport costs of coming to the clinic for each study visit. Participants who miss a study visit will continue to be followed up for both sample collection and vaccine administration where possible, with attempts made to contact them until such time as they would have completed the study.

### Data management

Data collection forms are double-entered by dedicated data entry staff into pre-coded EpiData V.3.1 files with built-in range and consistency checks. Entered data are validated monthly and then uploaded to a central Microsoft Access database, stored on a secure server. Immunology results are double-entered in a Microsoft Excel spreadsheet. NP culture results are entered in a Microsoft Access database and qPCR and microarray results exported from SentiNET into a Microsoft Excel database. The data collection forms and laboratory results are linked at the time of analysis.

### Statistical methods

#### Analysis of primary and secondary outcomes

For each of the two study questions, the primary objective is to compare a 2+1 schedule of (1) PCV10 and (2) PCV13, with a 3+1 schedule of PCV10. The primary outcome is the proportion of participants with serotype-specific antibody concentrations ≥0.35 µg/mL, 4 weeks post-primary series (at 5 months of age). Data from arms A and B are combined to form the three-dose post-primary series group. The primary analyses assess the non-inferiority of (1) two doses of PCV10 at 2 and 4 months of age (arm C) compared with three doses at 2, 3 and 4 months of age (arms A+B); and (2) two doses of PCV13 at 2 and 4 months of age (arm E) compared with three doses of PCV10 at 2, 3 and 4 months of age (arms A+B). The proportion of children achieving protective levels of serotype-specific IgG (≥0.35 µg/mL) 4 weeks post-primary series is determined for each of the 10 PCV10 serotypes. The non-inferiority margin is defined by a 10% difference in absolute risk. The serotype-specific risk differences (arms A+B/arm C) with 90% CIs are calculated using the Newcombe Score method and the null hypothesis rejected if the upper bound of the CI is <10%. Overall non-inferiority is declared if at least 7 of the 10 individual null hypotheses are rejected at a one-sided 5% level of significance. Secondary data analyses to address the primary objective include the ratio of GMCs post-primary series (arm C/arms A+B and arm E/arms A+B) with 95% CIs, and the booster response analysed by analysis of covariance, adjusting for pre-booster levels.

#### Analysis of key secondary objectives for study question 1

A single dose of PCV10 at 2 months of age (arm D) will be assessed for non-inferiority to three doses at 2, 3 and 4 months of age (arms A+B), as described for the primary objective.The impact of a booster dose on pneumococcal and NTHi carriage will be assessed at 12 months of age. Overall pneumococcal, capsular pneumococcal, PCV10 type and NTHi carriage rates will be determined. Proportions will first be compared between the 3+1 group (arm A) and the control group (arm F), using Fisher’s exact test. Where significant differences are found, rates will then be compared between the 3+0 group (arm B) and controls and between the 3+1 and 3+0 groups.

#### Analysis of key secondary objectives for study question 2

The immunogenicity of two doses of PCV10 or PCV13 will be compared in relation to the proportion of participants with serotype-specific antibody concentrations ≥0.35 µg/mL (to the 10 shared serotypes), 4 weeks post-primary series (at 5 months of age). A significant difference will be indicated by a 10% difference in absolute risk, comparing PCV10 (arm C) with PCV13 (arm E), and an overall difference will be declared if at least 7 of the 10 individual null hypotheses are rejected and the seven differences are in the same direction.The immunogenicity of a single dose of PCV10 or PCV13 will be compared, as described for the immunogenicity of two doses.

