## Objectives

This trial has been designed to answer two independent questions concurrently, relating to the evaluation of different schedules incorporating PCV10 and the comparison of PCV10 and PCV13:What is the optimal schedule for provision of EPI vaccines with the incorporation of PCV10; andHow do the responses to vaccination with PCV10 or PCV13 compare?

The primary endpoint for both study questions is the post-primary series immunogenicity. For this endpoint, data from arms A and B are combined, as they receive an identical three-dose primary series (see table 1 for a detailed description of the trial arms). The primary analysis for each study question is to assess non-inferiority of the post-primary series immunogenicity (in terms of the proportion of participants achieving protective levels of serotype-specific IgG of ≥0.35 µg/mL), using arms A+B as the comparator (see below for details). Non-inferiority is assessed for each of the 10 serotypes in PCV10, and an overall conclusion of non-inferiority drawn if found for at least 7 of the 10 serotypes.

**Table 1 T1:** Schedule of enrolment, interventions and assessments

Age (months)	2	3	4	5	6	7	9	9.5	10	12	18	19	24
Enrolment													
Informed consent	X										X*		
Eligibility assessment	X										X*		
Allocation	X												
Interventions													
PCV10—group A	X	X	X				X						
PCV10—group B	X	X	X										
PCV10—group C	X		X					X					
PCV10—group D	X				X								
PCV13—group E	X		X					X					
PCV10—group F											X		X
PCV10—group G													X
Assessments													
Demographics	X										X*		
Household characteristics	X										X*		
Nasopharyngeal swab	X				X		X			X	X		X
Blood sample—group A	X†			X			X		X		X†		
Blood sample—group B				X	X		X†		X		X†		
Blood sample—group C				X	X†		X		X		X†		
Blood sample—group D		X			X	X	X†				X†		
Blood sample—group E		X†		X			X		X		X†		
Blood sample—group F											X	X	X
Blood sample—group G											X	X	X
General health	X	X	X	X	X	X	X	X	X	X	X	X	X

*Group G only. Any events occurring before 18 months do not apply to group G.

†Each participant provides only one of these blood samples (the last 50 participants per group enrolled into groups A–E provide this blood sample at 18 months; the remainder provide it at the other time point).

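### The 5% one-sided error rate stated for the overall 7-of-10 non-inferiority conclusion is only the per-serotype level; the overall rule can err up to about 16% of the time per comparison

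*Protocol article*

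**What the plan says.** All references are to the Protocol article.

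- **Objectives** sets the form of the overall claim: "an overall conclusion of non-inferiority drawn if found for at least 7 of the 10 serotypes".
- **Analysis of primary and secondary outcomes** sets the serotype test. "The non-inferiority margin is defined by a 10% difference in absolute risk", and the risk differences "with 90% CIs are calculated using the Newcombe Score method and the null hypothesis rejected if the upper bound of the CI is <10" per cent. A two-sided 90% interval corresponds to one-sided 5%. The decision rule follows: "Overall non-inferiority is declared if at least 7 of the 10 individual null hypotheses are rejected at a one-sided 5% level of significance". No adjustment for counting 7 out of 10 is described.
- **Sample size** states the operating characteristics of the overall claim: "This sample size provides >99% power for the overall conclusion of non-inferiority with a 5% one-sided type I error rate". Serotype-level powers (83% to above 99%) come in a separate sentence.

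The rule applies to both primary comparisons: arm C against A+B, and arm E against A+B. The article does not define an overall null hypothesis and reports no simulated overall type I error.

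**The concern.** A 5% test of each component gives a 5% test of the combined claim only when every component must be rejected. Here three failures are allowed. The claim is that at least seven serotypes are non-inferior, so its natural null is that at most six are. Suppose exactly six are clearly non-inferior. They will nearly always be rejected, and the overall claim then needs just one false rejection among the other four, each with a 5% chance.

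Both primary conclusions rest on this count, and a reader of the Sample size section would take 5% as the risk of a wrong overall conclusion. Nor is the unfavourable region remote. The Introduction notes that antibody levels to 6B and 23F tend to be lower after two doses of CRM197-conjugated vaccines, and these serotypes also have the lowest assumed response rates. Weak serotypes could therefore use up part of the allowance of three failures.

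**Working it through.** **Inputs (Sample size section, unless noted)**

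- Planned sizes: "target group sizes of A=150, B=150, C=250, D=200, E=250 and F=200", so A+B = 300 and C = E = 250.
- Attrition: "the loss to follow-up rate is assumed to be 5% post-primary series". Evaluable: 300 × 0.95 = 285 and 250 × 0.95 = 237.5, taken as 237.
- Response rates: "the assumed probabilities of antibody concentration ≥0.35 µg/mL are 95% for serotypes 1, 4, 5, 7F, 9V, 14 and 19F"; 90% for 18C, 80% for 23F and 75% for 6B.
- Correlation: subject-level random intercept with SD 1.7 in a logistic model.
- Test: Newcombe two-sided 90% interval, upper bound below 10 points (Analysis of primary and secondary outcomes).

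**Step 1: reproduce the stated powers.** For 6B with equal true rates of 75%:

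SE = √[0.75 × 0.25 × (1/285 + 1/237)] = 0.0381

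power ≈ Φ(0.10/0.0381 − 1.645) = Φ(0.98) ≈ 83.7%

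The Farrington-Manning form gives 83.2% (6B), 87.7% (23F), 97.7% (18C) and 99.9% (the 95% serotypes). This matches the stated range of 83% to above 99%. Simulating ten correlated endpoints gives overall power of 99.98%, matching the stated figure of above 99%. The inputs are therefore read as the plan intended.

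**Step 2: overall error by arithmetic.** Let k serotypes lie exactly at the margin and the other 10 − k always be rejected. The claim is made if at least k − 3 of the k are falsely rejected. Under independence:

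- k = 4: 1 − 0.95⁴ = 18.5%
- k = 5: 1 − 0.95⁵ − 5 × 0.05 × 0.95⁴ = 2.3%
- k = 10: P(at least 7 of 10) ≈ 8 × 10⁻⁸

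**Step 3: overall error under the plan's correlation model.** Simulation with SD 1.7, 285 against 237, Newcombe 90% intervals. In every row the null is true. Serotypes not mentioned have zero true difference.

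| True state | Overall claim made |
|---|---|
| 18C, 23F, 6B and one 95% serotype at 10 points | about 16.4% |
| Four 95% serotypes at 10 points | about 14.8% |
| Same four as row 1, at 11 points | about 9.5% |
| Same four as row 1, at 12 points | about 4.8% |
| Same four as row 1, at 13 points | about 2.1% |
| Same four as row 1, at 15 points | about 0.6% |
| Same four as row 1 at 10 points, other six 5 points lower | about 6.4% |
| Five at 10 points | about 4.2% |
| All ten at 10 points | below 0.1% |

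Row 2 is lower than row 1 because 6B and 23F are then among the six that must be rejected, and their power is only about 83% and 88%. Simulation error is about √(0.16 × 0.84/10,000) = 0.4 points at 10,000 replicates. Each serotype at the margin is rejected about 5% of the time, as designed. Replacing Newcombe by Farrington-Manning moves the overall figure by about 0.1 point.

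**Step 4: what overall control would cost.** With four tests able to produce the one false rejection, 0.05/4 = 1.25% one-sided per serotype (two-sided 97.5% interval) brings the row 1 error to about 4.5%; under independence it is 1 − 0.9875⁴ = 4.9%. A 2.5% level would not suffice (8.9%; 9.6% under independence). The effect on overall power depends on the true differences, which are assumptions here:

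| True deficit, every serotype | 5% per serotype | 1.25% per serotype |
|---|---|---|
| 0 points | 99.98% | about 99.6% |
| 2 points | about 98% | about 80-81% |
| 3 points | about 88% | about 56% |

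**The case against.** **The 5% may have been meant per serotype.** The analysis section attaches the level to the individual hypotheses, and the Sample size sentence could be describing the test level used in the power simulation. This reading is possible and cannot be ruled out, since no overall null is defined. It does not remove the point: the sentence as printed ties 5% to the overall claim, with serotype-level figures given separately. Under this reading the wording needs correcting, and the overall error is then stated nowhere.

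**The 15-16% is a worst case.** This stands. A reader might infer that the overall claim simply has a 15-18% error rate, or that any schedule inferior on four serotypes would pass about three times as often as stated. The documents do not support either. The maximum needs exactly four serotypes at the margin and six clearly non-inferior, and the rate falls to about 5% once the four are 12 points lower. The 18.5% figure needs independence, whereas the plan assumes correlated serotypes. Type I error is nevertheless conventionally quoted as the maximum over the null, so 5% is not the right figure for the overall claim.

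**Tightening the serotype level is not free.** This also stands. A small loss of power holds only if all true differences are essentially zero, which a two-dose against three-dose comparison need not satisfy. Using 90% intervals for serotype statements and 97.5% intervals for the count could also report seven serotypes as non-inferior while the overall claim fails, against the rule in Objectives.

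**Conclusion.** The 5% stated for the overall conclusion is incorrect as worded; it is the level of each serotype test. Taking the overall null as at most six of ten truly non-inferior, the rule's maximum type I error is about 15-16% for each primary comparison under the plan's own inputs, and 18.5% under independence. It is about 5% or less if the four failing serotypes are 12 or more points below the comparator or if five are at the margin, and near zero if all ten are at the margin.

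The result rests on 285 against 237 evaluable infants, the assumed response rates, SD 1.7, and that definition of the null, which is inferred from the form of the claim. It does not show that the serotype tests are invalid, that the sample size is wrong, or that the 7-of-10 rule must be abandoned. The misstatement concerns the error rate of both primary conclusions, and restating it is sufficient.

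**What to change.** In Sample size and in Analysis of primary and secondary outcomes, state that the one-sided 5% level applies to each serotype, and that the overall 7-of-10 conclusion has a maximum type I error of about 16% for each primary comparison (C against A+B, and E against A+B). Add that this maximum arises with six serotypes clearly non-inferior and four at the margin. The cost is a sentence in each place; design, sample size and primary analysis are unchanged.

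Optionally, if the sponsor wants the overall claim held at 5%, report as a sensitivity analysis whether at least seven serotypes also meet the margin with two-sided 97.5% Newcombe intervals (1.25% one-sided each). The power for that stricter count is lower by under half a point if all true differences are zero (99.98 − 99.6 = 0.4), by about 17 points if every serotype is 2 points lower, and by about 32 points if 3 points lower (88 − 56). For that reason it is offered alongside the planned rule, not in place of it.
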